### Trial organization/coordination

The IMRT-HIT-SNT trial has been designed by the Department of Radiation Oncology, University of Heidelberg, and is carried out at the Heidelberg Ion Therapy Centre (HIT). It is an investigator-initiated trial; the Department of Radiation Oncology is responsible for co-ordination, overall trial management, registration (clinicaltrials.gov Identifier: NCT 01220752), database management, quality assurance, monitoring, and reporting.

### Investigators

Patients are recruited by the Department of Radiation Oncology.

### Adverse events

Adverse and serious adverse events are recorded using NCI common toxicity criteria for adverse events (CTCAE v.4). Acute radiation effects are defined as effects occurring within 90 days from beginning of radiotherapy. Late effects are defined as effects observed thereafter. Safety analysis is performed with respect to frequency of serious adverse events and adverse events stratified by organ system, severity, causality.

### Regular completion of the trial

Patient accrual is completed with inclusion of the last patient and should extend for approximately 4 years from trial initiation. Regular trial participation for each patient terminates 2 years post inclusion into the trial or the patient's death respectively.

### Discontinuation of treatment

• Patient wish

• Medical condition necessitating treatment termination and withdrawal of the patient from the trial

• Pregnancy

• Lack of compliance

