
Mucositis ≥ CTCAE°III is a very painful radiogenic acute toxicity leading to significant reduction of the patients' quality of life. In addition, higher grade mucositis may also lead to increased hospital admission for intensive supportive therapy including cost-intensive parenteral feeding. In addition, severe mucositis also leads to an increased number of therapy interruptions or even discontinuation of therapy and hence worsening o therapeutic outcome. In cases where additional chemotherapy is applied concomitantly, it is even more important to keep radiation-induced mucositis to a minimum to maintain compliance with the treatment regimen.

Both carbon ion therapy and IMRT have the potential to reduce normal tissue injury while allowing dose escalation within the tumour or prior tumour bed. The present trial (IMRT-HIT-SNT) was therefore designed to evaluate toxicity with special focus on mucositis ≥ CTCAE°III and efficacy in combined intensity-modulated RT and carbon ion boost.

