## Methods/design

### Study design

The IMRT-HIT-SNT trial is a prospective, non-randomized phase II feasibility trial evaluating acute mucositis ≥ CTCAE°III as the primary endpoint.

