### Study objectives

To evaluate feasibility and toxicity (with a focus on mucositis CTCAE °III) and efficacy of the treatment.

Incidence of mucositis ≥ CTC°III will be assessed as the primary endpoint of the trial, local control, disease-free survival, overall survival, toxicity (incl. mucositis CTCAE °I-II and late toxicity at 2 years post RT).

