**Figure 1 F1:**

**Trial flow chart**.

First follow-up examination including diagnostic, contrast-enhanced MRI will be carried out 6 weeks post completion of RT. Further controls including MRI are 3, 6, and 12 months thereafter, in 6 monthly intervals until 2 years post RT.

Patients are also encouraged to undergo regular check-ups incl. full ENT clinical examinations and/or ophthalmological examinations as applicable in regular intervals (figure 2). Performance state (Karnofsky-Index), therapy-associated side effects as well as potential intercurrent therapy of each patient are recorded on follow-up.

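### One discontinuation bullet merges a medically required stop of radiotherapy with leaving the trial, and no other section keeps such patients in follow-up for the secondary endpoints

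*Protocol article*

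**What the plan says.** The section Discontinuation of treatment is a list of four reasons with no further text. One reads "Medical condition necessitating treatment termination and withdrawal of the patient from the trial". The other three are the patient's wish, pregnancy and "Lack of compliance"; none of these mentions leaving the trial.

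Regular completion of the trial fixes the ordinary end of participation: "Regular trial participation for each patient terminates 2 years post inclusion into the trial or the patient's death respectively". Premature termination of the trial concerns closure of the whole study. The discontinuation list is therefore the only place that deals with an individual patient's early exit.

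The primary endpoint is short-term: Study design describes the trial as "evaluating acute mucositis ≥ CTCAE°III as the primary endpoint". After naming it, Study objectives lists "local control, disease-free survival, overall survival, toxicity (incl. mucositis CTCAE °I-II and late toxicity at 2 years post RT". These further outcomes depend on visits after treatment: a first examination with MRI 6 weeks after radiotherapy, and then "Further controls including MRI are 3, 6, and 12 months thereafter, in 6 monthly intervals until 2 years post RT".

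**The concern.** Stopping radiotherapy and ending a patient's participation are different events. A patient whose treatment is stopped can usually still be followed for survival, disease status and toxicity. A patient who has been withdrawn is normally not followed. By naming both in one phrase under a treatment heading, the bullet invites staff to withdraw a patient whose radiotherapy had to stop for a medical condition.

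At stake are the efficacy outcomes and late toxicity. The carbon ion fractions are given first, so a patient who stops during IMRT has already received the experimental component, and any late effect of it matters to the trial. If patients who stop for medical reasons do worse than the rest, losing them makes the reported local control and survival too favourable.

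**Working it through.** The bullet contains no figure to recompute, so the check is mainly a comparison of sections.

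1. **Does another section keep these patients in follow-up?** No. The 2-year term in Regular completion of the trial is given for regular participation only. The follow-up schedule is timed from completion of radiotherapy and does not mention patients who stop early. Equally, no section says that data collection ends for them.

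2. **What would be lost?** The section Adverse events says: "Acute radiation effects are defined as effects occurring within 90 days from beginning of radiotherapy". Later effects count as late. Late toxicity therefore lies after day 90, and local control and survival are followed to 2 years. For a patient withdrawn when treatment stops, most or all of this is still to come.

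3. **Would the loss be related to outcome?** The Background says that "severe mucositis also leads to an increased number of therapy interruptions or even discontinuation of therapy and hence worsening o therapeutic outcome". It also names a total dose above 65 Gy as prognostic for local control and survival, from a cited series in unresectable tumours. On the article's own way of adding dose, a patient who stops after k IMRT fractions has received 24 + 2k:
   - k = 12 (the 20th fraction overall): 24 + 2 × 12 = 48
   - k = 20: 24 + 2 × 20 = 64

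   So a stop at or before the 20th IMRT fraction leaves the patient below that threshold. Applying the threshold to a combined carbon ion and photon dose is an assumption. With that caveat, both statements suggest a worse prognosis for patients who stop early.

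4. **How large could the effect be?** The only related figure is the 10% drop-out allowance. It reproduces: 27 evaluable patients / (1 − 0.10) = 30. It belongs to the sample size for the mucositis endpoint and gives no reasons for drop-out, so it is not a rate of medical withdrawal. Purely as illustration, assume that w of 30 patients are withdrawn and that 80% of those retained are locally controlled at 2 years. The rate in all 30 then lies between 0.8(30 − w)/30, if none of the withdrawn is controlled, and [0.8(30 − w) + w]/30, if all are:

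| w | Retained | Lowest | Highest |
|---|---|---|---|
| 1 | 29 | 23.2/30 = 77.3% | 24.2/30 = 80.7% |
| 3 | 27 | 21.6/30 = 72.0% | 24.6/30 = 82.0% |
| 6 | 24 | 19.2/30 = 64.0% | 25.2/30 = 84.0% |

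Both w and the 80% are assumptions. The table shows only that the uncertainty grows quickly with each patient lost from a group of 30.

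**The case against.** The strongest reply is that the bullet sets no rule. It can be read as describing a condition serious enough to require both steps, and it does not say that every medical stop forces withdrawal. That reading is possible. But the list then has no entry for a medical condition that stops treatment and leaves follow-up possible, so the wording still needs to be clarified.

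A second reply is that a condensed article may leave follow-up after an early stop to the full protocol. That would excuse silence, but here the article expressly couples the two events.

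Third, the link to prognosis is only partly documented. The Background speaks of stops caused by severe mucositis, whereas a medical condition may be an unrelated illness. This stands, and is why the loss can be called plausibly informative but not shown to be so.

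A reader might also infer that everyone who stops radiotherapy early leaves the trial. The documents do not support this: three of the four reasons do not mention withdrawal, and their silence is not a defect in an article of this kind.

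**Conclusion.** The bullet merges the end of treatment with the end of study participation for medically required stops, and nothing else in the article separates them. Taken literally, it would cost the 2-year local control, survival and late-toxicity data of these patients, with a probable bias in the favourable direction. This is a modest point, worth making because the remedy is cheap.

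The size cannot be stated. A reader might take the w = 3 row above as a bias of 80.0 − 72.0 = 8 percentage points. The documents do not support that figure. It treats the whole drop-out allowance as medical withdrawal, assumes an 80% control rate, and supposes that all three lost patients fail; the same row also allows the reported rate to be 2 points too low. It further assumes that withdrawn patients drop out of a crude denominator, which the article does not prescribe. In a time-to-event analysis they would contribute until censoring. Bias from censoring related to prognosis could remain, but these proportions do not measure it.

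Nor should a reader infer that the trial's decision rule is undermined. That rule rests on acute mucositis, and a mucositis event that leads to the stop would already have been recorded.

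**What to change.** Reword the bullet in Discontinuation of treatment so that stopping radiotherapy is not in itself withdrawal from the trial. State that follow-up data continue to be collected to 2 years unless the patient withdraws consent to data collection. These data are survival and disease status, toxicity, and those scheduled follow-up examinations that remain appropriate for the patient. State also that these patients are kept in the local control and survival analyses.

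The clinical criteria for stopping treatment stay with the investigators, and the change should not require imaging after every stop.

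The cost is a short text change and a few extra follow-up contacts on a schedule that already exists. Sample size and decision rule are untouched.

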### Premature termination of the trial

The trial can be prematurely closed or suspended by the LKP in following cases:

• Medical or ethical reasons relevantly affecting the risk-benefit relationship,

• Difficulties in recruitment of subjects suggest unjustifiable prolongation of the study timeline,

• Previously unexpected adverse events (in respect of their nature, severity, duration or outcome) occur with unjustifiable frequency,

• Expected adverse events occur with an unexpectedly high incidence,

• Relevant superiority of patients in one treatment arm of a comparable clinical trial,

• Legal authorities' decision

The Ethics Committee (EC) and the competent regulatory authorities will be informed about premature closure of the trial. Furthermore, the Ethics Committee(s) and competent regulatory authorities themselves may decide to stop or suspend the trial.

If the trial is closed prematurely, the trial material such as completed, partially completed, and blank CRFs will be returned to the coordinating investigator.

All involved investigators have to be informed immediately about a cessation or suspension of the trial. The decision is binding on all trial centers and investigators.

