### Sample size/number of subjects

Incidence of mucositis CTC°III in the reported data was 14.1% for IMRT to similar total doses [3]. As described before, IMRT and carbon ion therapy promise a reduction of mucositis rates as compared to previous reports. We assume the new therapy to be clinically irrelevant if the incidence of mucositis ≥CTCAE°III is higher than 30% whereas the experimental therapy is clinically feasible and warranting further investigation if the rate of mucositis ≥CTCAE°III is less than 10% and hence more than 90% of patients do not experience a mucositis ≥CTCAE°III. Using Simons Two-stage-Design (α = 0.05; Power 80%) a sample size of 30 patients was caluclated assuming a drop out rate of 10%. In the first stage, a maximum of 2 out of 6 patients may show a mucositis ≥CTCAE°III, and 5 out of 27 patients in total [23].

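### Cheap improvement: close accrual at the event that exceeds a mucositis limit, because no stated rule stops stage 2 once the trial can only be negative

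*Protocol article*

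**What the plan says.** Protocol article, Sample size/number of subjects: the trial uses a Simon two-stage design with α = 0.05 and 80% power. A rate of mucositis of grade III or higher above 30% counts as unacceptable, and a rate below 10% as worth pursuing. The limits are: "In the first stage, a maximum of 2 out of 6 patients may show a mucositis ≥CTCAE°III, and 5 out of 27 patients in total". The section does not say in words what happens to accrual when a limit is exceeded, although naming the design implies a decision after stage 1.

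Protocol article, Premature termination of the trial: "The trial can be prematurely closed or suspended by the LKP in following cases". Six reasons follow. Neither mucositis limit is among them. The closest is "Expected adverse events occur with an unexpectedly high incidence", with no figure attached.

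Protocol article, Regular completion of the trial: accrual ends with the last patient, over about 4 years. The two stages are not mentioned.

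**The concern.** The primary endpoint is itself a harm. The sixth evaluable patient with severe mucositis settles the trial: whatever happens to the remaining patients, the final limit of 5 has been passed. The written rule looks at the count at 6 patients and again at 27. If the true rate is near the unacceptable 30%, the sixth event will usually arrive well before patient 27. Patients included after it receive a regimen that has already failed the trial's own toxicity criterion, and they cannot change the primary result. What is at stake is patient exposure; the error rates hardly enter.

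**Working it through.** **Inputs.** Rates of 30% (unacceptable) and 10% (acceptable), α 0.05, power 80%, 30 patients with 10% dropout, and limits 2/6 and 5/27, all from Sample size/number of subjects. The 90-day window for acute effects is from Adverse events, and the 4 years of accrual from Regular completion of the trial. All patient counts below are evaluable patients.

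**1. The plan's own sample size.** 27/0.90 = 30, so the stated total reproduces. An exact search for the Simon design that minimises expected size at 30% also gives 6 and 27 patients. Its limits are 1/6 and 4/27, with α 0.049 and power 0.804. The printed limits are each one event higher. That is a separate matter, so both sets are carried through.

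**2. Printed limits, looks at 6 and 27 only, true rate p = 30%.**

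- P(stage 2 reached) = P(Bin(6, p) ≤ 2) = 0.744.
- E[N] = 6 + 21 × 0.7443 = 21.63.
- P(success) = Σ P(Bin(6, p) = x) × P(Bin(21, p) ≤ 5 − x), x = 0, 1, 2 = 0.1176 × 0.3627 + 0.3025 × 0.1984 + 0.3241 × 0.0856 = 0.130.
- P(failure in stage 2) = 0.7443 − 0.1304 = 0.614, which is 82.5% of the trials that reach stage 2.

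**3. Stop at the event that exceeds a limit.**

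- Stage 2: an exact recursion over patients 7 to 27 gives an average of 7.54 patients still to come when the sixth event occurs. Saving: 0.614 × 7.54 = 4.63.
- Stage 1: the third event can fall on patient 3, 4 or 5, leaving 3, 2 or 1 patients. Saving: 0.0270 × 3 + 0.0567 × 2 + 0.0794 × 1 = 0.27.
- E[N] = 21.63 − 4.63 − 0.27 = 16.73. Stage-2 stopping alone gives 17.00.
- Expected severe cases (0.30 × E[N]) fall from 6.5 to 5.0.

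**4. α and power.** Accrual stops only on paths that already end in failure, so no success is lost or gained. P(success) stays at 0.130 (rate 30%) and 0.943 (rate 10%) with the printed limits, and at 0.049 and 0.804 with 1/6 and 4/27.

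**5. Outcome lag.** 30 patients in 4 years is 7.5 a year, and 7.5 × 90/365 = 1.8, so about 2 patients enter while an outcome is pending. Adding up to 2 patients after each exceedance, never beyond 27, gives E[N] of about 18.4. Stage-2 failures then spare about 5.7 patients each. If accrual also pauses after patient 6 until stage 1 is read, E[N] is about 18.1.

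**6. Both sets of limits, true rate 30%.**

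| | 2/6, 5/27 | 1/6, 4/27 |
|---|---|---|
| E[N], looks at 6 and 27 | 21.6 | 14.8 |
| E[N], immediate stop | 16.7 | 10.6 |
| E[N], stop with 2-patient lag | 18.4 | 12.5 |
| P(failure in stage 2) | 0.61 | 0.37 |
| Patients spared per stage-2 failure, no lag | 7.5 | 8.3 |

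**7. If the stage-1 stop were not enforced.** α becomes P(Bin(27, 0.3) ≤ 5) = 0.136 instead of 0.130 with the printed limits, or P(Bin(27, 0.3) ≤ 4) = 0.059 instead of 0.049 with 1/6 and 4/27.

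**The case against.** The strongest case against is that nothing is wrong. A Simon design has one interim look, and continuous stopping in stage 2 is an optional extra. That is correct, and the point is therefore offered as an improvement.

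A reader might also infer three stronger things, none of which the document supports:

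- *That accrual is not tied to the limits at all.* The sample-size section names a two-stage design and gives a stage-1 maximum, and naming the design carries the stage-1 stop. The discretionary wording under Premature termination governs the reasons listed there. It does not say that the stage-1 limit may be overridden.
- *That enrolment does run on to 27 after the final limit is exceeded.* No sentence says so; this would be an inference from silence. The authority to close for excess mucositis exists through the adverse-event and risk-benefit reasons. What is absent is a numerical trigger.
- *That leaving the stage-1 limit off the closure list is a defect.* This is a condensed article, and the mechanics of the interim decision may stand in the full protocol.

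Two further objections bear on size. The best-case savings assume that each outcome is known before the next inclusion. This stands, which is why the lagged figures are given alongside. The change also costs information on local control and survival. This stands too, but only in trials already negative on toxicity.

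**Conclusion.** The point holds as a cheap improvement. The written rule checks the count at 6 and 27 patients and leaves any other closure to judgement without a number, so no stated rule closes accrual in stage 2 once failure is certain.

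At a true rate of 30% with the printed limits, a binding stop saves 21.6 − 16.7 = 4.9 evaluable patients per trial on average, or about 21.6 − 18.4 = 3.2 with a 2-patient lag. The lagged figure is cautious: it lets inclusions run past patient 6, while the 21.6 assumes a pause there.

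If the true rate is the hoped-for 10%, the stop rarely acts. About 1.6% of trials fail in stage 1 and 4.1% in stage 2, and E[N] changes only from 26.7 to 26.5.

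The results rest on independent patients with a constant event rate, steady accrual, and 27 evaluable patients. The α effect of not enforcing the stage-1 stop is small and does not carry the argument. That the printed limits give an exact α of 0.130 against the stated 0.05 is a larger and separate problem, and it lends no weight here.

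**What to change.** Add one sentence under Sample size/number of subjects and repeat it under Premature termination of the trial: accrual closes as soon as the number of patients with mucositis of grade III or higher exceeds the stage-1 limit among the first 6 evaluable patients, or exceeds the final limit at any time in stage 2. Mark it as binding, separate from the discretionary reasons.

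The sentence concerns inclusion of new patients only. It needs no change to sample size, α or power, and it works with whichever limits are finally adopted. The cost is fewer patients for local control, disease-free survival and overall survival when the regimen has already failed its toxicity criterion.

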### Ethics, informed consent, and safety

The final protocol was reviewed by the ethics committee of the University of Heidelberg Medical School (S-319/2009). The trial complies with the Helsinki Declaration in its recent German version, the Medical Association's professional code of conduct, principles of Good Clinical Practice (GCP) guidelines and the Federal Data Protection Act. It will be carried out in keeping with local legal and regulatory requirements. It is also subject to authorization by the German radiation protection authority (Bundesamt für Strahlenschutz: = BfS). Medical confidentiality and Federal Data Protection Act will be followed. Written informed consent is obtained from each patient in oral and written form.

## Discussion

Sinonasal tumours are rare malignancies of the nasal cavity and paranasal sinuses. Preferred treatment would generally be complete surgical resection. Due anatomical site and proximity to critical structures surgical treatment is very complex and clear margins are rarely achieved. Therefore, the majority of patients will undergo RT either because of involved surgical resection margins or technical inoperability.

Outcome with adjuvant or definitive RT however has so far been hampered by high rates of accompanying toxicity. Modern radiotherapy techniques such as IMRT and image-guided RT (IGRT) have improved toxicity. Despite these sophisticated new techniques, it remains challenging to apply sufficient doses to the tumour in order to improve control rates.

This phase II trial was designed to evaluate the combination of 50 Gy IMRT plus 24 GyE carbon ion boost to a total dose of 74 GyE with respect to toxicity and control rates. To our knowledge, this is the first prospective trial evaluating this treatment regimen in sinonasal cancers.
